**Methods and design::**

Eighty prediabetes individuals will be recruited for this study. Eighty prediabetes individuals will be divided into lifestyle intervention group and viscera massage + lifestyle intervention group by a simple random method. Each group will have 40 individuals. The manipulation of the viscera massage + lifestyle intervention group will be mainly carried out through rubbing the abdomen, kneading abdomen, vibrating abdomen, and pressing the abdomen, 30 minutes per time, once a day, with 2 days off every 5 days. Lifestyle interventions will be performed by combining pushing healthy lifestyle guidance information through Wechat application and giving face-to-face advice together daily. The lifestyle intervention group will receive healthy lifestyle intervention only. All the intervention will be conducted for 4 weeks. Weight, body mass index (BMI), waist circumference, waist-to-hip ratio, and waist-to-height ratio will be measured at the last day of every week. Triglycerides, total cholesterol, low-density lipoprotein cholesterol, high-density lipoprotein cholesterol, fasting blood-glucose, 2-hour post-meal blood glucose (2hPG) and glycosylated hemoglobin, fasting insulin and insulin resistance index will be tested at the first day and last day of the intervention course. The fecal samples of subjects will be gathered at the first day and last day of the intervention course and will be performed 16S rRNA gene sequencing and metagenomic detection. Finally, the effect and potential mechanism of viscera massage on prediabetes will be discussed in combination with all the results.

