#### Body composition measurements

2.11.1

Weight, BMI, waist circumference (WC), WHR, and WHtR will be measured by a special study nurse at the first day of the whole intervention and last day of every week. BMI was calculated using body weight and height measured with bare feet and in minimal clothing using a stadiometer and an electronic scale. Waist circumference will be measured at the body midsection (iliac crest), which is between the lowest point of the ribs and the highest point of the pelvis, while the participants were in a calm, exhaling position, with their legs 25 to 30 cm apart. Hip circumference will be measured at the horizontal circumference of the rear most prominent part of the hip. WHR will be calculated by WC/hip circumference. WHtR will be calculated by WC/height.

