#### Blood sample

2.11.2

Blood samples will be taken from each participant twice—one before the first treatment, and the other following the last treatment. Measurements will include triglycerides, total cholesterol, low-density lipoprotein cholesterol, and high-density lipoprotein cholesterol, FBG, 2hPG, and HbA1c, fasting insulin and HOMA-IR.

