#### Fecal samples

2.11.3

Fecal samples from the participants will be obtained before and after the intervention. Samples will be collected using the special feces collection kit. All fecal specimens will be stored in the fridge at –80 °C before and after the intervention, and then will be performed for 16S rRNA gene sequencing and metagenomic detection.

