#### Statistical method

2.11.5

SPSS23.0 statistical software will be used for statistical analysis for all the data generated. Chi-square test will be used for enumeration data. Paired *t* test will be used for the comparison of measurement data before and after the treatment. One-way analysis of variance (ANOVA) will be used for comparison between the groups, with *P* < .05 as difference and *P* < .01 as significant difference.

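### The between-arm test is a one-way ANOVA with no baseline term, although every body and blood outcome has a pre-treatment value; ANCOVA would be at least as precise and would remove the observed baseline difference from the estimate

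*Protocol article*

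**What the plan says.** Section 2.11.5 (Statistical method) gives measurement data two tests. Within an arm: "Paired *t* test will be used for the comparison of measurement data before and after the treatment". Between arms: "One-way analysis of variance (ANOVA) will be used for comparison between the groups". The thresholds follow: "with *P* < .05 as difference and *P* < .01 as significant difference". No covariate is named. The section does not say whether the ANOVA is applied to end-of-course values or to changes from day 1.

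The baseline values will exist:

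- Blood outcomes (section 2.11.2): "Blood samples will be taken from each participant twice—one before the first treatment, and the other following the last treatment". The abstract agrees that they "will be tested at the first day and last day of the intervention course".
- Body measures (section 2.11.1): taken "at the first day of the whole intervention and last day of every week". The abstract mentions only the weekly readings; section 2.11.1 adds the day-1 reading.
- Fecal samples (section 2.11.3) are also taken before and after, but the figures below do not cover the sequencing outcomes.

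Section 2.2 (Setting) plans 40 people per arm, with odd enrolment numbers going to one arm and even numbers to the other, and describes no stratification.

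**The concern.** A one-way ANOVA has group as its only factor, so with two arms it is the two-sample t test. The plan therefore has one test that uses baseline but compares no arms, and one that compares the arms but, as worded, has no baseline term.

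Two things are at stake. The first is precision: where a person's day-1 and end values are correlated, the day-1 value explains part of the end-value variance, and leaving it out widens the interval for the arm difference. The second is conditional error: if the arms differ at day 1, part of that difference carries into an unadjusted end-value comparison. A comparison of changes over-corrects for it instead.

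**Working it through.** **Inputs.** From the documents: two arms, 40 per arm (section 2.2), and P < .05 (section 2.11.5). Assumed, because the documents do not give them: a two-sided test, equal SDs at day 1 and end, a true arm difference of 0.4 SD, and a baseline-to-end correlation ρ from 0.3 to 0.8, with higher values for weight.

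**The plan's own figure.** Section 2.2 states 36 per arm without effect size, SD or power, so it cannot be reproduced. Solving backwards with Δ = √(2/36) × (1.96 + 0.84), it fits a difference of about 0.66 SD at 80% power, two-sided. That neither confirms nor refutes the 36, and nothing below depends on it.

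**Variance of the arm difference**, relative to ANOVA on end values:

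- end values: 1
- change scores: 2(1 − ρ)
- ANCOVA: 1 − ρ²

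The ratio of ANCOVA to change scores is (1 − ρ²) / [2(1 − ρ)] = (1 + ρ)/2, which never exceeds 1. Nor does 1 − ρ². Apart from the one degree of freedom spent, ANCOVA is therefore no less precise than either version of the ANOVA.

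**Power** for 0.4 SD with 40 per arm, from the noncentral t with noncentrality 0.4 / √(v × 2/40), where v is the relative variance:

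| ρ | v, changes | v, ANCOVA | Variance cut, ANCOVA vs end values | Power, end values | Power, changes | Power, ANCOVA |
|---|---|---|---|---|---|---|
| 0.3 | 1.40 | 0.91 | 9% | 42% | 32% | 46% |
| 0.5 | 1.00 | 0.75 | 25% | 42% | 42% | 53% |
| 0.7 | 0.60 | 0.51 | 49% | 42% | 63% | 70% |
| 0.8 | 0.40 | 0.36 | 64% | 42% | 80% | 84% |

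At ρ = 0.9 the change-score and ANCOVA variances are 0.20 and 0.19, so the choice between them hardly matters.

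**Weight as an example** (assumed SD 12 kg). The difference detectable with 80% power is (t.975 + t.80) × 12 × √(v × 2/40), with t.975 = 1.99 and t.80 = 0.85:

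- end values: 7.6 kg
- changes: 2.41 kg at ρ = 0.95, 1.52 kg at ρ = 0.98
- ANCOVA: 2.38 kg at ρ = 0.95, 1.51 kg at ρ = 0.98

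**Baseline differences.** If allocation behaved as random, the day-1 difference between arms would have a standard error of √(2/40) = 0.22 SD. A gap above 0.3 SD in either direction would then have about an 18% chance for each outcome. Given a gap of +0.3 SD, the expected error in the estimated effect is:

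| ρ | End values (0.3ρ) | Changes (−0.3(1 − ρ)) | ANCOVA |
|---|---|---|---|
| 0.5 | +0.15 SD | −0.15 SD | about 0 |
| 0.7 | +0.21 SD | −0.09 SD | about 0 |
| 0.9 | +0.27 SD | −0.03 SD | about 0 |

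Simulation of 20,000 trials at each of these correlations agrees with these errors. It also shows an overall type I error near 5% for all three methods.

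**The case against.** The strongest reply is that section 2.11.5 never says end values are compared. If the ANOVA is run on changes, baseline is already used and much of the loss disappears: at ρ = 0.7 and 0.8 the comparison is 63% against 70% and 80% against 84%, not 42% against 70% and 84%. This stands, and the size must be given under both readings. It does not remove the point, because ANCOVA remains at least as precise and change scores still carry a baseline difference, with the opposite sign.

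Second, the correlation is unknown and may be low where it matters clinically. Section 2.5 (Diagnostic criteria) restricts entry on fasting and 2-hour glucose, which can lower their baseline-to-end correlation. This also stands: at ρ = 0.3 the variance cut against end values is only 9%.

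Third, covariate adjustment is often left to an analysis plan, which is not shown. This carries less weight, since the article itself names the test, and a one-way ANOVA admits no covariate.

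A reader might infer three stronger things that the documents do not support:

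- *That the trial certainly discards much of its precision, worst of all for weight and waist.* This needs both end values and a high correlation. The fall in detectable weight difference from 7.6 kg to 2.4–1.5 kg applies only if end values are compared; against changes it vanishes.
- *That the stated test is invalid.* It keeps its 5% error rate.
- *That any baseline difference would be due to chance.* Section 2.2 allocates by odd or even enrolment number, and section 5 concedes that the design is not completely randomized. Differences may be systematic, and a baseline covariate does not cure that.

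**Conclusion.** The point holds as a fault of efficiency and of conditional error. Section 2.11.5 fixes an arm comparison without a baseline term, while sections 2.11.1 and 2.11.2 supply a pre-treatment value for every body and blood outcome.

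The size depends on the assumed ρ and on which quantity the ANOVA compares. For 0.4 SD with 40 per arm, the power gain from ANCOVA at ρ = 0.3/0.5/0.7/0.8 is about 3/11/27/41 percentage points against end values and 14/11/7/4 points against changes. It may be small for fasting and 2-hour glucose if end values are compared, and is negligible at ρ of 0.9 or more if changes are compared. That ANCOVA is no worse in precision does not depend on which ρ is right. The change is worth making, but the trial's validity does not turn on it.

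**What to change.** In section 2.11.5, replace the one-way ANOVA with ANCOVA for each continuous body and blood outcome: end-of-course value as response, arm as factor, and the same outcome's day-1 value as covariate. Report the adjusted mean difference between arms with its 95% CI. SPSS, already named in that section, runs this in its general linear model procedure. This wording also settles whether end values or changes are analysed.

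The cost is one sentence of analysis text and one degree of freedom per outcome, with no new data. The odd/even allocation in section 2.2 is a separate matter that this change does not repair.

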### Setting

2.2

The patients will be recruited from the Department of tuina, Affiliated Hospital of Changchun University of Chinese Medicine, Hongqi First Community Health Service Center, Chaoyang District and Hongqi Second Community Health Service Center, Chaoyang District. Patients participating in the trial will be screened strictly according to the diagnostic criteria, inclusion criteria, and exclusion criteria. The sample size estimation will be based on the clinical calculation formula employed for small sample size. The estimate sample size is (n = 36). So, the therapeutic effect could be evaluated by the sample size of >36 in each group. In this study, 80 individuals will be recruited by simple random method and divided into two groups, 40 individuals in each group.

The researcher of the project will record the subject's basic information (such as date of birth, age, sex, and address) and answer questions patient involved in the trial. After completed the recruitment, individuals involved will be assigned a trial study serial number, also the patient's unique identification number, according to the order of enrollment, until the total numbers (n = 80) are all allocated. The odd-numbered individual was divided into the lifestyle intervention group, with the even-numbered individual the viscera massage + lifestyle intervention group. After clinical evaluation, blood and stool sampling, viscera massage therapy will be adopted.

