## Discussion

3

Prediabetes is defined as blood glucose levels above normal but below diabetes thresholds, with hyperglycemia and insulin resistance the major threads.^[7]^ Prediabetes includes IFG, IGT, and IFG+IGT. The IFG subjects always have high hepatic insulin resistance with almost normal values in skeletal muscle, while high insulin resistance in skeletal muscle with only modest changes in liver insulin sensitivity is commonly in IGT subjects.^[3]^ The incidence of prediabetes is rising as the prevalence of obesity increases globally.^[7]^ So, in this trial, we will select not only the common indicators of prediabetes, such as FBG, 2hPBG, and HbA1c, but also the indicators associated with obesity, like weight, BMI, WC, WHR, WHtR, and blood lipid level. And studies have found that a combination of WC and WHtR may be a better clinical utility than BMI and WHR in identifying individuals with cardiometabolic risk factors.^[21]^ Fasting insulin and HOMA-IR will be used to test the level of insulin resistance. Through the proposed clinical trial, the effect of AM on prediabetes and obesity will be further verified.

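### As written, the between-group test takes triglycerides, fasting insulin and HOMA-IR untransformed and without their day-1 values, which costs precision but not validity

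*Protocol article*

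**What the plan says.** Section 2.11.5 (Statistical method) assigns tests by type of data, not by variable. Within groups: "Paired *t* test will be used for the comparison of measurement data before and after the treatment". Between groups: "One-way analysis of variance (ANOVA) will be used for comparison between the groups". The thresholds are given "with *P* < .05 as difference and *P* < .01 as significant difference", without saying whether the tests are one- or two-sided. No variable is excepted. The section mentions no log transformation and no baseline covariate, and does not say whether the ANOVA uses final values or changes.

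Section 2.11.2 (Blood sample) puts the three measures among that data: "Measurements will include triglycerides, total cholesterol, low-density lipoprotein cholesterol, and high-density lipoprotein cholesterol, FBG, 2hPG, and HbA1c, fasting insulin and HOMA-IR". It also shows that a baseline exists for each of them: "Blood samples will be taken from each participant twice", before the first treatment and after the last. The Discussion gives two of the three a specific job: "Fasting insulin and HOMA-IR will be used to test the level of insulin resistance".

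**The concern.** Two features of the stated comparison may waste information.

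- **Baseline.** Each participant supplies a day-1 value of every blood measure, but a one-way ANOVA of final values ignores it. If day-1 and final values correlate, the part of the between-person spread that the day-1 value explains stays in the error term.
- **Scale.** HOMA-IR is by definition a scaled product of fasting glucose and fasting insulin. In overweight or obese entrants, a long upper tail is plausible for it, for insulin and for triglycerides. If spread grows with level and a benefit acts proportionally, a comparison of arithmetic means is less precise than a comparison of logs.

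At stake is the chance of detecting a real effect on three of the nine blood measures, including both that are meant to show insulin resistance, and the width of their confidence intervals.

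**Working it through.** **The plan's own figure.** The article gives no SD, effect size or power for these three measures, so there is no plan figure to reproduce.

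**Inputs from the article.** 40 per arm (section 2.2); a 5% level (section 2.11.5), taken as two-sided; two arms, so that one-way ANOVA equals the two-sample t test; one day-1 and one final value (section 2.11.2).

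**Inputs assumed.** Lognormal values with log-SD s = 0.4, 0.5, 0.6 or 0.7; a 25% reduction (ratio 0.75); correlation 0.6 between log day-1 and log final values.

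**Step 1. What s means.** CV = √(exp(s²) − 1), which gives 42%, 53%, 66% and 80%.

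**Step 2. Cost of the raw scale for small effects.** Efficiency relative to the log scale = s²/(exp(s²) − 1), which gives 0.92, 0.88, 0.83 and 0.78.

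**Step 3. Power on the log scale, by hand.** The effect is |ln 0.75| = 0.288 and the unadjusted standard error is s√(2/40). At s = 0.5 the standard error is 0.112, the ratio is 2.57, and power ≈ Φ(2.57 − 1.96) = Φ(0.61) = 73%. The baseline covariate multiplies the standard error by √(1 − 0.6²) = 0.8. The ratio becomes 3.22 and power ≈ Φ(1.26) = 90%. Simulation with t distributions gives 72% and 89%.

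**Step 4. All four analyses, simulated (20,000 trials per cell).**

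| Analysis of final value | s = 0.4 | 0.5 | 0.6 | 0.7 |
|---|---|---|---|---|
| Raw, unadjusted (as written) | 86% | 67% | 50% | 36% |
| Log, unadjusted | 89% | 72% | 57% | 44% |
| Raw, day-1 covariate | 96% | 83% | 65% | 49% |
| Log, log day-1 covariate | 98% | 89% | 75% | 62% |

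**Step 5. Splitting the gain.** From the first row to the last, the gain is 12 / 22 / 25 / 26 points. The covariate alone, on the raw scale, gives 10 / 16 / 15 / 13. The log scale then adds 2 / 6 / 10 / 13. Without the covariate, the log scale adds 3 / 5 / 7 / 8 (rounded; about 2.5 at s = 0.4). At s = 0.3, raw and log both have about 99% power unadjusted.

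**Step 6. If the ANOVA is meant for changes.** With the same inputs, raw changes give 66 / 48 / 35% power at s = 0.5 / 0.6 / 0.7, and log changes 81 / 66 / 53%. Both stay below log with covariate (89 / 75 / 62%).

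**Step 7. Validity.** With no true difference, the raw-scale test rejects in 4.5 to 5.0% of simulated trials over CV 30 to 100%.

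**The case against.** The strongest case against the point has four parts.

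- **The scale is inferred.** Section 2.11.5 names tests, not a scale. A t test or ANOVA on logs is still a t test or ANOVA, and a full protocol or SAP that is not shown may specify one. This stands, so the point concerns what the published sentence says when read naturally and is not proof that logs will not be used.
- **The skewness is undocumented.** No SD, CV or distribution is given, and the 25% effect and the correlation of 0.6 are assumed too. This also stands. With low skewness the log scale gains almost nothing.
- **Two changes are bundled.** Much of the difference between the first and last rows of the table comes from the covariate. That is correct, and it is why the rows are separated. The covariate needs no assumption about skewness, only a useful correlation with data already collected.
- **The arithmetic mean is a legitimate target.** A difference in clinical units is a defensible summary, so preferring a ratio is a choice, not the correction of an error.

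Two stronger readings are tempting, and the article supports neither.

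- A reader might infer that the raw scale takes the trial below its stated need, since section 2.2 says "the therapeutic effect could be evaluated by the sample size of >36 in each group" and efficiency below 0.9 makes 40 act like fewer than 36. But the 36 comes with no outcome, effect size, SD, power or scale, so it cannot be tied to these measures. If it had been computed from a raw-scale SD, the inefficiency would already be in it.
- A reader might also infer that a few high values decide the result. In simulation over CV 30 to 100%, the two highest of 40 values carry 31 to 52% of the within-group sum of squares on the raw scale, against 21% on the log scale. They weigh more and make the estimate less stable, but the error rate holds.

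**Conclusion.** The point holds as a matter of efficiency and is minor. The comparison fixed in section 2.11.5 is valid, but it sets aside the day-1 value and, on its natural reading, the scale on which these three measures probably behave best. Under the assumptions listed, the better analysis raises power by 12 to 26 points over log-SD 0.4 to 0.7. The share due to the log scale depends on a skewness that the article does not document; the share due to the covariate depends only on the day-1 to final correlation. The text shown names no primary outcome, and fasting insulin and HOMA-IR overlap, so the effect on the trial's overall conclusion is limited.

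**What to change.** Add one sentence to section 2.11.5: for triglycerides, fasting insulin and HOMA-IR, the arms will be compared by ANCOVA of the natural log of the final value with the natural log of the day-1 value as covariate, and the effect reported as a ratio of geometric means with a 95% CI. Fix this before any data are seen, and do not make it depend on a normality test. If an unseen SAP already says so, the published sentence only needs to be brought into line with it.

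The cost is a log transform and a covariate in the software already named. No extra samples or visits are needed. The small downside is that effects on these outcomes are read as percentage differences and not in laboratory units.

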## Introduction

1

Prediabetes is an intermediate metabolic state between normoglycemia and diabetes, including impaired fasting glucose (IFG), impaired glucose tolerance (IGT), and the mixed-status (IFG+IGT).^[1]^ Approximately 5–10% of people with prediabetes will become diabetic each year, and up to 70% of individuals with prediabetes will eventually develop diabetes in their lifetime.^[2]^ The U.S. National Health and Nutrition Examination Survey suggests that 35% of US adults over 20 years of age and 50% of those over 65 had prediabetes in 2005 to 2008 based on fasting glucose or glycosylated hemoglobin (HbA1c) levels.^[3]^ Within the Asian region, the prevalence of prediabetes among adults reaches 50% in China, with Indians 18.9%, and Malays 22.6% respectively.^[4,5]^ Prediabetes is more prevalent than diabetes^[6]^ and pre-diabetes is more prevalent in women (21.9%) and urban dwellers (21.5%).^[4]^ Without intervention, prediabetes often progresses to diabetes and prediabetes is associated with increased risk of cardiovascular disease, cancer, renal disease, and dementia.^[7]^ People with prediabetes may have concomitant damage to end organs, such as eyes, kidneys, blood vessels, and the heart that are traditionally considered to be complications of diabetes.^[3]^ Lifestyle modification, including weight loss, dietary changes, and increased physical activity, play a major role in controlling prediabetes. Significant evidence also supports the effectiveness of a combination of lifestyle modification and pharmacologic therapy, such as metformin, in delaying the onset of diabetes.^[4]^ But lifestyle interventions are often challenging and with poor compliance.^[8]^ People are always afraid of the side effects of drugs. As a non-invasive treatment with no side effects, AM, also called viscera massage in China, has been used to treat prediabetes as well as the associated overweight and obesity. Mechanical AM and manual AM had been used to reduce cellulite,^[9]^ thigh and infraumbilical circumference,^[9]^ arm and post-partum abdominal, and flank subcutaneous fat deposits,^[10]^ improve skin laxity,^[10]^ and serum lipids.^[11]^ Manual AM also can enhance the effectivity of cryolipolysis treatment.^[12]^ As prediabetic individuals are often overweight or obese,^[13]^ AM has been used to manage prediabetes, and can significantly reduce the levels of fasting blood-glucose (FBG) and 2 hours postprandial blood glucose (2hPBG) in patients with prediabetes, with the decrease of 2hPBG more significant.^[14]^ In order to uncover the underlying mechanism of AM, several animal experiments had been carried out. AM can alleviate glucose and lipid metabolism disorder by regulating of AMPK/Glut4 signaling chain, the gene transcription and protein expression of Nuclear factor kappa beta and interleukin-6 in skeletal muscle,^[15,16]^ gut microbiota and bile acid metabolism^[17]^ in T2DM rats. Prediabetes is intertwined with the increasing incidence of metabolic syndrome and obesity. Prediabetes and T2DM has similar pathophysiology. However, there are few clinical studies and mechanism studies specially on prediabetes.

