
The gut microbiota has been recognized as an important factor in the development of metabolic diseases such as prediabetes, T2DM, and obesity, and is considered an endocrine organ involved in the maintenance of energy homeostasis and host immunity.^[18]^ The intestinal microbiota species may interact with host metabolism through metabolite-mediated stimulation of enteric hormones and other systems outside of the gastrointestinal tract, such as the endocannabinoid system. Individuals with prediabetes have aberrant intestinal microbiota characterized by a decreased abundance of the genus Clostridium and the decreased abundance of bacterium *A. muciniphila*.^[19]^ Based on previous studies and the important role of gut microbiota in metabolism, the proposed clinical trial will determine the possible effects of AM on prediabetes by evaluating the FBG, 2-hour post-meal blood glucose (2hPG), HbA1c, fasting insulin, insulin resistance index (HOMA-IR), blood lipid, BMI, waist-to-hip ratio, and waist-to-height ratio (WHtR), and will explore the mechanism of viscera massage on prediabetes from the perspective of intestinal microbiota.

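### Fourteen outcomes share a two-tier P-value rule with no primary outcome named, so the false-positive chance is far above 5% and n = 36 is tied to no comparison

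*Protocol article*

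**What the plan says.** Section 2.11.1 lists five body measures: "Weight, BMI, waist circumference (WC), WHR, and WHtR will be measured by a special study nurse". They are taken "at the first day of the whole intervention and last day of every week". Section 2.11.2 lists nine blood measures, taken before the first and after the last treatment: "Measurements will include triglycerides, total cholesterol, low-density lipoprotein cholesterol, and high-density lipoprotein cholesterol, FBG, 2hPG, and HbA1c, fasting insulin and HOMA-IR". Section 2.11.3 adds stool samples, which "then will be performed for 16S rRNA gene sequencing and metagenomic detection".

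The end of the Introduction says the effect will be determined "by evaluating the FBG, 2-hour post-meal blood glucose (2hPG), HbA1c, fasting insulin, insulin resistance index (HOMA-IR"), followed by lipids and body measures. The text reviewed ranks no outcome; section 2.4 was not in it. The Discussion only groups outcomes by theme: FBG, 2hPBG and HbA1c as common indicators of prediabetes; weight, BMI, WC, WHR, WHtR and lipids as obesity-related; insulin and HOMA-IR for insulin resistance.

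Section 2.11.5 prescribes paired t tests for change within a group and one-way ANOVA between groups, "with *P* < .05 as difference and *P* < .01 as significant difference". Section 2.2 takes n = 36 from an unnamed formula for small samples and concludes that "the therapeutic effect could be evaluated by the sample size of >36 in each group"; 40 per group are to be recruited. Both the Abstract and the Discussion speak of verifying the effect.

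**The concern.** A trial that sets out to verify an effect needs one comparison whose result decides the question. Here the decision rule is attached to every outcome alike, so nothing in the text stops a single favourable result among 14 from being reported as the effect of massage.

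The two-tier wording adds a second ambiguity. A result at P = .03 is a difference but not a significant one, and the text does not say which tier counts as success.

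The sample size has the same gap. A number per group has meaning only for a stated outcome, effect, variability, power and alpha. Without these, the statement that the therapeutic effect can be evaluated cannot be checked and supports no particular conclusion.

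**Working it through.** **Inputs from the article**
- Outcomes: 5 body (2.11.1) + 9 blood (2.11.2) = 14. The microbiota tests are left out because their number is not stated.
- Between-group test: ANOVA with two groups, which is equivalent to a two-sample t test (2.11.5).
- Thresholds: .05 and .01 (2.11.5).
- Size: 36 per group estimated, 40 per group recruited (2.2).

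**Assumptions.** Tests are two-sided. There is one between-group test per outcome, at the end of treatment. Correlations between outcomes are mine; the article gives none.

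**1. The plan's own figure.** The 36 cannot be reproduced, because no inputs are given. Several input sets lead to it (two-sample, normal approximation, d = √(2/36) × (z for alpha + z for power)):

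| Alpha | Power | Standardised difference giving n = 36 |
|---|---|---|
| two-sided .05 | 80% | 0.66 |
| two-sided .05 | 90% | 0.76 |
| one-sided .05 | 80% | 0.59 |
| two-sided .01 | 80% | 0.81 |

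The first row is √(2/36) × (1.960 + 0.842) = 0.2357 × 2.802 = 0.66. The article selects none of these.

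**2. False-positive chance over 14 outcomes, independent.** The chance is 1 − (1 − α)^14.
- α = .05: 1 − 0.95^14 = 0.512
- α = .01: 1 − 0.99^14 = 0.131

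**3. The same with correlated outcomes.** Simulation of 20,000 null trials, 40 per group, two-sample t tests, equal pairwise correlation:

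| Assumed correlation | At least one P < .05 | At least one P < .01 |
|---|---|---|
| 0.3 | 44% | 12% |
| 0.5 | 35% | 9% |
| 0.7 | 25% | 7% |

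An assumed block structure, with weight–BMI, WC–WHtR and insulin–HOMA-IR as near-duplicates, gave about 41% and 10%, inside the same range.

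**4. Counting only the Discussion's three prediabetes indicators.** 1 − 0.95^3 = 0.143 if independent.

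**5. What the size detects for one outcome.** Two-sample t test, two-sided .05, 80% power, noncentral t, no baseline adjustment: 0.67 SD with 36 evaluable per group and 0.63 SD with 40. The 0.67 exceeds the 0.66 in step 1 only because the t distribution replaces the normal.

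**The case against.** **Left to the analysis plan.** Multiplicity procedures and the ordering of secondary outcomes are often set in an analysis plan that is not shown. That is fair, and their absence alone is not the point. What stands is that the article itself prints the decision rule and the sample size without saying which outcome either serves.

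**The outcomes are not all equal.** The Discussion groups them, and the Introduction's list omits weight and WC, leaving 12. Equal weight is therefore an inference from the lack of ranking. But grouping is not ranking, and the three prediabetes indicators alone still give about 14%.

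**Stronger readings the text does not support:**
- A reader might infer that a chance finding is likely. Only independence passes 50%, and independence cannot hold: BMI is computed from weight and WHtR from WC.
- A reader might count the body measures at each of the four weekly readings: 5 × 4 + 9 = 29 tests. The article sets a weekly measurement schedule but never says the groups are compared each week.
- A reader might argue that 36 per group is too small at the .01 tier. That presumes 36 was derived at 5% with 80% power, which is not stated. By the t calculation, 36 fits two-sided .01 with 80% power equally well at about 0.83 SD.

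**Conclusion.** The point holds in this form: the plan aims to verify an effect, names no primary outcome, applies one two-tier rule to 14 outcomes, and gives a sample size tied to none of them. The chance of at least one false between-group P < .05 is about five to nine times the nominal 5% at correlations of 0.7 to 0.3, with 51% as the upper end. The stricter tier does not bring it back to 5% over that range. These figures rest on assumed correlations and one test per outcome; within-group paired tests and microbiota tests are not counted. The article does not show that 36 is the wrong number, only that it cannot be checked.

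**What to change.** Before any outcome is compared by group:
- **Section 2.11.** Name one primary outcome from the prediabetes indicators already collected. Week-4 2hPG or FBG are examples. The Introduction reports a cited massage study "with the decrease of 2hPBG more significant", which favours 2hPG, but section 2.5 admits IFG-only participants with 2hPG below 7.8 mmol/L, for whom that measure is not raised. The investigators should choose in view of the expected IFG/IGT mix.
- **Section 2.11.5.** State one success rule: the between-group difference at week 4, adjusted for baseline, at two-sided alpha 0.05. Delete the two tiers. Label the remaining outcomes secondary (tested in a fixed order or by Holm) or exploratory, with estimates and confidence intervals.
- **Section 2.2.** Tie the size to the primary outcome. If the original inputs are known, give them. In any case state what the size detects: about 0.67 SD with 36 evaluable per group, or 0.63 SD with 40, at 80% power and two-sided 5%, unadjusted. Present these as properties of the size, not as the assumption behind it.

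This needs no new visit, assay or participant. The price is that claims on the non-primary outcomes become weaker.
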